## Abstract

**Purpose:**

The evidence regarding the (cost-)effectiveness of sacral neuromodulation (SNM) in patients with therapy-resistant idiopathic slow-transit constipation is of suboptimal quality. The Dutch Ministry of Health, Welfare and Sports has granted conditional reimbursement for SNM treatment. The objective is to assess the effectiveness, cost-effectiveness, and budget impact of SNM compared to personalized conservative treatment (PCT) in patients with idiopathic slow-transit constipation refractory to conservative treatment.

**Methods:**

This study is an open-label, multicenter randomized controlled trial. Patients aged 14 to 80 with slow-transit constipation, a defecation frequency (DF) < 3 per week and meeting at least one other Rome-IV criterion, are eligible. Patients with obstructed outlet, irritable bowel syndrome, bowel pathology, or rectal prolapse are excluded. Patients are randomized to SNM or PCT. The primary outcome is success at 6 months (DF ≥ 3 a week), requiring a sample size of 64 (*α* = 0.05, *β* = 0.80, 30% difference in success). Secondary outcomes are straining, sense of incomplete evacuation, constipation severity, fatigue, constipation specific and generic quality of life, and costs at 6 months. Long-term costs and effectiveness will be estimated by a decision analytic model. The time frame is 57 months, starting October 2016. SNM treatment costs are funded by the Dutch conditional reimbursement program, research costs by Medtronic.

**Conclusions:**

The results of this trial will be used to make a final decision regarding reimbursement of SNM from the Dutch Health Care Package in this patient group.

**Trial registration:**

This trial is registered at clinicaltrials.gov, identifier NCT02961582, on 12 October 2016.

**Electronic supplementary material:**

The online version of this article (10.1007/s00384-018-2978-x) contains supplementary material, which is available to authorized users.

## Background

Functional constipation (FC) is a functional bowel disorder with predominating symptoms of difficult, infrequent, or incomplete defecation, defined by the Rome-IV criteria [1, 2]. Abdominal pain and/or bloating may be present, but should not be the predominant symptoms as the Rome-IV criteria for irritable bowel syndrome should not be met [1]. The prevalence of FC ranges between 16 and 19.2% in Europe [3–5].

Approximately 1% of chronic FC patients are refractory to conservative treatment and are treated at the hospital. A subset of approximately 15 to 30% of these patients is diagnosed with slow-transit constipation [6]. Slow-transit constipation is characterized by slow transit of feces and is due to dysmotility of the colon. There is no presence of outlet obstruction. However, the etiology of dysmotility remains unexplained [7, 8]. Slow-transit constipation is often assessed by using radiopaque markers or nuclear scintigraphy to evaluate colonic transit [1]. Treatment for slow-transit constipation consists of lifestyle changes such as a total daily intake of 20–30 g of dietary fibers, increasing water intake, behavioral changes (pelvic floor physiotherapy and biofeedback therapy), laxatives (bulking, osmotic, stimulant, and softening), pro-secretory agents (linaclotide, lubiprostone, and prucalopride in adults), and retrograde bowel irrigation [1, 9, 10].

Surgical options performed in this patient group are subtotal colectomy and colostomy [6, 11, 12]. However, the risk of morbidity and mortality of these interventions are high, 20 and 2.6% respectively [9, 13]. Hence, patients often continue conservative treatment instead of undergoing surgical intervention, resulting in an impaired mental and physical quality of life (QOL) with restrictions in daily activities and productivity [14].

Sacral neuromodulation (SNM) is a minimally invasive surgical technique that delivers direct electrical stimulation to the sacral nerves and has been proven effective in patients with urinary disorders and fecal incontinence [15–18]. Although SNM is considered potentially effective in patients with chronic slow-transit constipation, conflicting results are shown. Available studies are heterogeneous in terms of study population and methodology. A subset of the studies focuses on patients with slow-transit constipation only. However, most studies also take into account patients with different etiologies of constipation. Two randomized controlled trials (RCT) compared SNM to sham-stimulation instead of conservative treatment. These RCTs showed no significant difference in success rates between SNM and sham-stimulation (*n* = 53 and *n* = 36 respectively) [19, 20]. On the other hand, non-randomized studies of suboptimal quality found positive success rates varying from 29 to 63% in favor of patients treated with SNM [15, 21–24]. Up until now, there is no evidence regarding cost-effectiveness of SNM as a treatment modality for patients with slow-transit constipation. Therefore, as stated in the Cochrane review, more high-quality trials are needed to get more insight in the (cost-)effectiveness of SNM in this particular patient group [25].

Besides the Cochrane review, the Dutch Health Care Institute published a report stating that there is insufficient evidence of high methodological quality to conclude that SNM compared to conservative treatment is effective in slow-transit constipation [26]. As a result, SNM is not currently reimbursed by the health insurance. To gain more insight in the (cost-)effectiveness of SNM, the Dutch Ministry of Health, Welfare and Sports decided to conditionally reimburse treatment for patients participating in this RCT from October 1st 2016 until 30th June 2021 [27]. Next to the RCT, a prospective cohort study will be conducted monitoring the safety and effectiveness of SNM. At the end of the conditional reimbursement, June 2021, the Ministry will make a final decision regarding reimbursement of SNM. This paper describes the study protocol of the No.2-trial assessing the (cost-)effectiveness of SNM in patients with idiopathic slow-transit constipation refractory to conservative treatments. The protocol is written in accordance with the Standard Protocol Items: Recommendations for Interventional Trials (SPIRIT) checklist and figure (Fig. 1 and online resource supplementary file 1).

**Fig. 1 Fig1:**
[figure not shown]
Standard Protocol Items: Recommendations for Interventional Trials (SPIRIT) figure. ^a^ t4 will only be assessed in patients in the SNM group who still have the pulse generator at 12-month follow-up (dashed arrow); ^b^ all outcomes will be assessed except for resource use; ^c^ only constipation severity and generic (HR)QOL will be assessed

## Methods/design

### Study objectives

The primary objective is to assess the effectiveness of SNM compared to personalized conservative treatment (PCT) on treatment success at 6 months, in patients with idiopathic slow-transit constipation who are refractory to conservative treatment. Secondary objectives are to assess costs, cost-effectiveness, and budget impact of SNM compared to PCT.

### Study design

This study is a multicenter, open-label, and pragmatic randomized controlled trial (RCT). Recruited patients will be randomized to either SNM or PCT. Two centers in the Netherlands are currently recruiting participants for this study: the Maastricht University Medical Center (MUMC+) and the Groene Hart Hospital in Gouda. The Emma Children’s Hospital/Academic Medical Center in Amsterdam, the national referral center of patients under 18, is closely involved in the inclusion of the trial. Medtronic is partner in this project, funding the research costs (10% of total costs). The RCT has been registered at clinialtrials.gov identifier NCT02931582.

Parallel to the RCT, a prospective cohort study will be conducted to study and monitor the safety and effectiveness of SNM. Patients with a completed 6-month follow-up period randomized to the PCT group of the RCT or eligible patients who are referred when the inclusion period of the RCT has ended, are also offered SNM treatment. In the prospective cohort study, defecation frequency, constipation severity, and generic quality of life will be assessed. This prospective cohort study is registered at clinialtrials.gov identifier NCT02961465.

### Study population and recruitment

The study population consists of adolescents (14–17 years) and adults (18–80 years) with idiopathic slow-transit constipation refractory to conservative treatment. Patients will be referred to one of the participating centers by their (pediatric) gastroenterologist, surgeon, or general practitioner. The inclusion and exclusion criteria assessed during the screening visit are shown in Table 1. All patients will fill out a 3-week defecation diary to assess compliance to the Rome-IV criteria for idiopathic constipation. Patients will be asked to report defecation frequency, type of bowel stimulation (natural/laxatives/irrigation), presence of straining, sense of complete evacuation, sensation of anorectal obstruction, time spent on the toilet, impairment of daily activities, and presence of bloating and pain. Further diagnostic tests will include a defecography to exclude possible outlet obstruction and a colonic transit time measurement using radio-opaque markers to assess potentially delayed colonic transit time [28]. Eligibility will be confirmed during an outpatient appointment and patients will be informed regarding the study. If patients are willing to participate, written informed consent will be obtained during an outpatient appointment with the researcher.

**Table 1 Tab1:** Inclusion and exclusion criteria to assess patient eligibility

Inclusion criteria	Exclusion criteria
• An average DF of < 3 per week	• Diagnosed with obstructed outlet syndrome
• Meet at least 1 other criterion of the Rome-IV criteria* for functional constipation	• Diagnosed with irritable bowel syndrome
• Refractory to conservative treatment	• Congenital or organic bowel pathology
• Age between 14 and 80 years	• Rectal prolapse
• Diagnosed with slow-transit constipation	• Anatomical limitations preventing placement of an electrode
*Rome-IV criteria for FC [1]: In ≥ 25% of defecations:	• Skin and perineal disease with risk of infection
• Straining	• Previous large bowel/rectal surgery
• Lumpy or hard stools	• Stoma
• Sensation of incomplete evacuation	• Coexisting neurological disease
• Sensation of anorectal obstruction	• Significant psychological comorbidity
• Manual maneuvers to facilitate defecation	• Being/attempting to become pregnant during study follow-up

*DF* defecation frequency, *FC* functional constipation

### Randomization

After written informed consent, patients will be randomized according to the principle of minimization in a 3:2 ratio to SNM or PCT, using the online randomization database ALEA (ALEA software, TenALEA consortium, Amsterdam, the Netherlands), programmed by the Clinical Trial Center Maastricht (CTCM). Potentially confounding factors that will be used for minimization are study site, age, and gender. As SNM, a surgical intervention, is compared to conservative (medical) treatment, blinding to treatment allocation of patients and medical staff is not possible.

### Sacral neuromodulation

Patients randomized in the SNM group will undergo a 4-week stimulation test period by a tined lead procedure (TLP). Detailed operative procedures for SNM have been described elsewhere [29]. The temporary quadripolar tined lead *(InterStim 3889 or 3093, Medtronic Inc., MN, USA)* will be connected to the external stimulator *(InterStim Verify 3531, Medtronic Inc., MN, USA)*. If successful, the quadripolar lead will be attached to an implantable pulse generator *(Interstim 3058, Medtronic Inc., MN, USA*). The operative procedures will be conducted under local or general anesthesia. Success of the TLP test period is defined as a DF ≥ 3 as measured by a 3-week defecation diary which is also used to assess eligibility for the RCT.

Patients with an implanted pulse generator have scheduled appointments at 4 weeks, 2, 3, 6, and 12 months. Patients will be asked to limit the use of additional conservative treatments for constipation such as laxatives and colonic irrigation. If patients use conservative treatment, they will be asked to document it.

### Personalized conservative treatment

Patients in the PCT group will be treated at their referring center according to their normal personalized treatment algorithm. The received treatments will be recorded. To assess the primary outcome, an outpatient appointment will be planned 6 months after inclusion. Patients will then be offered SNM treatment as a part of the parallel prospective cohort study. Figure 2 shows the flow diagram of patients entering the study.

**Fig. 2 Fig2:**
[figure not shown]
Overview of the RCT and the prospective cohort study

### Primary and secondary outcomes

The primary outcome is treatment success at 6 months. Treatment success is defined as an average defecation frequency (DF) of ≥ 3 a week, based on a 3-week defecation diary. Patients with an average DF of < 3 a week are considered not successfully treated.

Secondary outcomes are (1) the proportion of patients with a 50% reduction in the proportion of defecations with straining, (2) the proportion of patients with a 50% reduction in the proportion of defecations with a sense of incomplete evacuation, (3) constipation severity, (4) fatigue, (5) constipation specific (health-related) quality of life ((HR)QOL), (6) generic (HR)QOL, (7) adverse events and complications, (8) resource use and costs, (9) cost-effectiveness, and (10) budget impact.

### Data collection and instruments

A 3-week defecation diary will be completed during the screening period/baseline (t0), 4-week follow-up (equal to the TLP test period in the SNM group) (t1), and at 3- (t2) and 6-month (t3) follow-up. Clinical and (HR)QOL secondary outcomes will be measured at the same time points. Resource use and costs will be assessed at t0, t2, and t3. In patients in the SNM group who still have the pacemaker at 12-month follow-up, the DF, constipation severity, generic (HR)QOL, and adverse events and complications will be assessed (t4).

#### Reduction in proportion of defecations with straining and defecations with a sense of incomplete evacuation

The proportion of defecations with straining and/or defecations with a sense of incomplete evacuation will be derived from the data in the 3-week defecation diary. The reported proportion of defecations with straining and/or a sense of incomplete evacuation will be compared to the proportion of defecations with straining and/or a sense of incomplete evacuation at baseline. Patients will be divided into two groups: (1) ≥ 50% reduction in the proportion of defecations with straining and/or a sense of incomplete evacuation and (2) < 50% reduction in the proportion of defecations with straining and/or a sense of incomplete evacuation.

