### Sample size calculation

The sample size calculation is based on the proportion of patients with treatment success at 6-month follow-up (primary endpoint). An absolute difference in success rate of 30%, with success rates of 35 and 5% for SNM and PCT respectively, is considered clinically relevant. The sample size required to detect this difference with a two-sided Fisher’s exact test equals 64 patients in total (alpha 0.05, power of 80 and 5% drop-out rate). With a randomization ratio of 3:2, 38 patients will be randomized to SNM and 26 patients will be randomized to PCT.

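### The responder rule for straining and incomplete evacuation can be read as a composite, and it counts patients with none of the symptom at baseline as non-responders

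*Protocol article*

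**What the plan says.** Under *Primary and secondary outcomes*, the first secondary outcome is "1) the proportion of patients with a 50% reduction in the proportion of defecations with straining" and the second is "the proportion of patients with a 50% reduction in the proportion of defecations with a sense of incomplete evacuation". They carry separate numbers.

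The section headed *Reduction in proportion of defecations with straining and defecations with a sense of incomplete evacuation* turns them into a rule. The sentence that sets the comparison with baseline begins "The reported proportion of defecations with straining and/or a sense of incomplete evacuation will be compared to the proportion". The next sentence forms two groups, at least 50% and less than 50% reduction, with the same and/or wording in each. There is no third group and no limit to patients who have the symptom.

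Table 1 sets the entry condition: a defecation frequency below 3 per week and "Meet at least 1 other criterion of the Rome-IV criteria". Five such criteria are listed, of which straining and incomplete evacuation are two. The diary records the two symptoms as separate items (*Study population and recruitment*).

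*Statistical analysis* prescribes intention to treat, counts drop-outs as failures, imputes missing values, and compares dichotomous secondary outcomes by adjusted logistic regression.

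**The concern.** Two features of the stated rule cause trouble.

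First, the and/or wording leaves open whether there are two outcomes or one proportion built from both symptoms. In an open-label trial that choice should be closed before results are seen.

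Second, the rule is a relative reduction from baseline applied to everyone, while a patient can be eligible without having the symptom. A patient who starts at 0% has nothing to halve, whichever treatment is given, and the only group left is the one with less than 50% reduction. Such patients add non-responders to both arms and pull the two responder rates together. At stake is how the first two secondary outcomes are read: a real effect on straining or incomplete evacuation would look smaller than it is among the patients who can benefit.

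**Working it through.** **The plan's own figure.** The article gives no figure for these two outcomes. Its only sample size concerns the primary outcome: "An absolute difference in success rate of 30%, with success rates of 35 and 5% for SNM and PCT respectively", "alpha 0.05, power of 80 and 5% drop-out rate". Full enumeration of the two-sided Fisher test at 35% vs 5% gives power 0.810 with 36 + 24 = 60 patients. Allowing for 5% drop-out, 60 / 0.95 = 63.2, so 64. The figure is reproduced and is not in dispute.

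**Do the readings differ?** A frequency below 3 per week over 3 weeks means at most 8 defecations. Take a constructed patient with 8 defecations in each diary. At baseline, both symptoms occur in 8/8. At 6 months, straining occurs in 2/8 and incomplete evacuation in the other 6/8.

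| Reading | Baseline | 6 months | Reduction | Class |
|---|---|---|---|---|
| Straining alone | 8/8 | 2/8 | 75% | responder |
| Incomplete evacuation alone | 8/8 | 6/8 | 25% | non-responder |
| Either symptom | 8/8 | 8/8 | 0% | non-responder |
| Both in the same defecation | 8/8 | 0/8 | 100% | responder |

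The example shows that the readings can disagree. It does not show how often they would.

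**Zero baseline.** The relative reduction is (p0 − p6) / p0, with p0 and p6 the proportions at baseline and 6 months. At p0 = 0 it is undefined, and since p6 cannot be below 0, no reduction can occur.

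Can eligible patients have p0 = 0? There are 2^5 − 1 = 31 ways to meet at least one of the five criteria. Of these, 2^4 − 1 = 15 do not include straining, and 2^3 − 1 = 7 include neither straining nor incomplete evacuation. This counts combinations, not patients.

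Missing the criterion means below 25% of defecations, which is not the same as 0%. With 4 or fewer defecations in the diary, one symptomatic defecation is already at least 25%, so below 25% means exactly 0%. With 5 to 8, a patient below 25% has 0 or 1 symptomatic defecation (1/8 = 12.5% to 1/5 = 20%), and with 1 a response is still possible.

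**Dilution.** Let z be the share of patients at 0%, equal in both arms in expectation because it is fixed before randomisation. If they count as non-responders, each rate is multiplied by 1 − z. Assume responder rates of 40% and 15% among patients with the symptom (25 points):

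- z = 10%: 36.0% vs 13.5%, difference 22.5 points (about 6 of 64 patients at 0%)
- z = 20%: 32.0% vs 12.0%, difference 20.0 points (about 13 of 64)
- z = 30%: 28.0% vs 10.5%, difference 17.5 points (about 19 of 64)

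**Empty diary at 6 months.** Here the proportion is 0/0. Assuming Poisson counts at r defecations per week, the chance is exp(−3r): 22% at 0.5, 5% at 1, and 1.1% at 1.5. The documents give no distribution of frequencies below 3 per week, so these figures only show how strongly the answer depends on r.

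**The case against.** The strongest reply is that and/or is shorthand for one rule applied to each symptom in turn. The section heading names both symptoms, the outcome list numbers them separately and the diary records them separately. This stands as a likely intention. A reader might infer that the protocol defines a composite and so contradicts itself outright; the text does not go that far. It is ambiguous, and the ambiguity matters because the readings can classify a patient differently.

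A second reply is that handling rules belong in the full protocol or analysis plan, which are not shown. For the empty diary this is fair: silence in a condensed article is no fault, and a rule is proposed below only so that the corrected definition is complete. For the zero baseline it is only partly fair, because the article does state a rule and that rule puts every patient into one of two groups. An undefined ratio might instead be treated as missing and imputed, but the text does not say so, and imputation cannot give a real reduction to a patient who starts at 0%.

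Three stronger inferences are not supported:

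- That everyone who enters on another criterion is barred from responding. Only a baseline of exactly 0% does that.
- That empty diaries are known to fall mainly in the conservative-treatment arm. This is plausible under the planned success rates, but no figure in the documents measures it, and diaries also record bowel movements stimulated by laxatives or irrigation.
- That a count model is needed. Such a model gives no weight to a patient without defecations, so it would not solve that problem.

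Finally, the dilution is conservative: it hides benefit and does not create a false positive.

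**Conclusion.** The point holds as a correction to two secondary outcomes. The and/or wording needs to be reconciled with the outcome list, and the two-group rule does not suit patients who have none of the symptom at baseline.

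The difference is diluted in proportion to the share of such patients: 2.5 to 7.5 points off an assumed 25-point difference, for an assumed share of 10% to 30%. Both the share and the responder rates are assumptions. If nearly all patients have both symptoms at baseline, the loss is close to nil. The direction, toward a smaller difference, follows from the rule itself provided that these patients are counted as non-responders.

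The primary outcome and the sample size do not depend on any of this.

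**What to change.** In the section that defines the two outcomes:

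1. Define them separately, as in the outcome list, and delete and/or. For each symptom, a responder has a reduction of at least 50% from baseline in the share of defecations with that symptom. This also settles the small difference between a 50% and an at-least-50% reduction.
2. Analyse each outcome in randomised patients whose baseline proportion for that symptom is above 0%. This subset is fixed before randomisation, so the comparison remains a randomised one. Report by arm how many patients it leaves out.
3. Class a 6-month diary with no defecations as non-response. This agrees with the plan's treatment of drop-outs as failures and keeps 0/0 from being imputed or counted as improvement.

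The planned logistic regression can stay. A model for counts of symptomatic defecations is optional and not part of this correction.

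The cost is wording and somewhat fewer patients: at the assumed shares of 10% to 30%, about 58 to 45 of 64 would remain for each outcome (64 × 0.9 = 57.6; 64 × 0.7 = 44.8). No new data are needed. The change should be made before results by arm are seen.
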